### Study objectives

The F0 of singing and its impact on neonatal brain development remains under-explored, particularly in the context of NICU environments. Current literature lacks detailed insights into how F0 variations, influenced by the biological sex and kinship of the singing source, affect the short-term neurophysiological responses of premature infants. Therefore, this exploratory study is developed as a complementary ‘single-arm’ extension of the randomized controlled trial (RCT; clinicaltrials.gov unique identifier: NCT06398912), aiming to address this research gap by isolating and further examining the neurophysiological mechanisms identified in the original RCT protocol. Specifically, this single-arm study focuses exclusively on the intervention group structure to investigate how different F0 profiles from human voices across various kinship dynamics (i.e., mother, father, male, and female music therapists) influence the brain activity of NICU infants.

The rationale and value for following this presentation approach at this stage (acknowledging of course the inherent limitations of this approach such as the absence of a direct comparison group and weaker causal interpretations) is twofold. First, and most importantly, reporting the single-arm protocol design and its preliminary data alone contributes significantly to the broader field by offering a rigorous methodological template, which can guide future research and intervention designs in similarly sensitive neonatal settings. Second, it allows for a detailed examination of individual and within-subject EEG response patterns to take place, providing nuanced insights that might be obscured by group-level analysis typical in RCTs. Therefore, we believe the current approach is scientifically justified, as it forms a critical foundation for subsequent comprehensive analyses within the context of our broader RCT.

Based on the above, the primary research question of the study reported here is: *Does a structured sound and music-based intervention, delivered by four different facilitators (mother, father, male and female music therapist) as determined by their fundamental frequency (F0) and kinship, result in a differentiated short-term electroencephalographic effect footprint in NICU infants?*

Our research hypotheses are as follows:

- *H1*: We hypothesize that when premature newborns are exposed to a live singing intervention provided by their mother (high fundamental frequency – biological kinship) compared to the father (low fundamental frequency – biological kinship) or an unrelated male/female music therapist, they show statistically more visible short-term positive oscillatory differentiations in their brain activity.

- *H0*: We assume that there is no interaction between the fundamental frequency and the kinship profile (mother, father, man, woman) in the infant’s reactions, and that neither the fundamental frequency nor the human profile has a primary effect.

To answer the research question and study its hypotheses, this study will utilize electroencephalography (EEG) to monitor and analyze the brain activity of NICU infants. By comparing EEG patterns across different music delivery conditions of F0 and kinship source (i.e., music facilitators), the findings are expected to provide valuable insights that can be leveraged to enhance neurodevelopmental outcomes in premature infants.

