### The fundamental frequency of singing

In the context of the NICU, understanding the technical features of the singing voice, including its fundamental frequency (F0) as distinct from pitch, becomes increasingly vital, not only due to the auditory sensitivity of premature infants but also because of the developing nature of their central nervous system, which is highly susceptible to the variability of external stimuli as they grow older.

The fundamental frequency (measured in Hertz) refers to a physical property of sound waves – specifically, the number of vibrations per second produced, for example, by the violin string or, in our case, the vocal cords [64–65]. Pitch, on the other hand, is the perceptual correlate of fundamental frequency; it describes how the brain interprets and perceives the fundamental frequency [64]. While F0 is an objective measurement, pitch is a more subjective experience; however, for most periodic sounds, the fundamental frequency closely corresponds to the perceived pitch [64–65]. As a result, F0 is often used as a proxy for pitch in acoustic analysis and research.

Given the critical role of fundamental frequency (F0) in shaping the auditory environment for infants, particularly in a singing context, it is important to understand the differences in F0 between male and female voices. These differences, driven by anatomical factors such as the length of the vocal tract and the size of the laryngeal cavities, result in male voices typically having a lower F0 – around 100–120 Hz – compared to the higher F0 of female voices, generally in the 200–220 Hz range [66–68]. Such distinctions may influence how infants respond to structured sound stimuli, especially in light of the well-documented human sensitivity to voice discrimination based on biological sex [69]. The fundamental frequency serves as the foundation upon which harmonic structures are built, guiding the singing experience and creating a scaffold for the infant’s brain to process the embedded complex auditory information. These differences in F0, therefore, may not only influence how infants respond to the singing environment in the NICU but may also convey biological and kinship-specific cues that can affect neural functioning and development in this sensitive population.

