Secondly, recent research, including a study by Restin et al. [72], indicates that incubators can be significant sources of noise, especially in the open environment of the NICU floor. To mitigate this issue, we plan to use an open cot/radiant warmer (as depicted in Fig 3) in the dedicated room when applicable, or alternatively, bring the entire incubator into the room. This approach will help minimize or eliminate noise from the incubator that might reach the infant. As an additional precaution to all the above, a dB measuring device will be also stationed in the dedicated room, outside the incubator where applicable, to monitor noise levels throughout the intervention.

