In regard to the singing stages, as stated above, all facilitators will be asked to sing at the same distant location from the cot, maintaining in this way consistent spatial sound parameters of stimulus delivery. For the first stage of the singing part (NoteA), each facilitator will be given a tuning fork (a forked acoustic component that produces sound upon impact and quickly silences) tuned to the musical note A (440 Hz) and asked to sing based on its produced sound the musical note A as best as they can. All facilitators will need to repeat the specific note *ad libitum* at any possible and convenient to them frequency that corresponds to this specific note (i.e., A2: 110 Hz; A3: 220 Hz; A4:440 Hz; A5:880 Hz) over 60 seconds at this stage. The tuning fork has been chosen to be used as it is a safe acoustic accessory for accurately reproducing the tone the facilitator needs to hear as an acoustical template when inserting it into their ear, ensuring at the same time that the infant will not be able to hear it and be affected by it.

For the second singing stage (Song), each facilitator will need to sing *a cappella* a complex acoustic stimulus with organized sounds in the form of a lullaby, specifically created and composed for the study by a professional musician and music therapist (a member of the research team). This lullaby was aimed to have a unique structure and acoustic information composition adhering to the known scientific evidence related to infants’ sound and music perception capabilities [96,97]. The song lasts 90 seconds and features a soft melodic line, gentle rhythm, simple harmonies in a minor key, and soft vocal timbre, influenced by folk characteristics found in Greek lullabies. Its tempo is expected to be approximately 60–75 beats per minute, following the rhythm of the seconds hand of the clock found on site as best as possible for consistency of delivery.

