### Outcomes and statistical analysis

To rigorously evaluate the effects of our live singing intervention, we decided to employ a series of advanced statistical methods tailored to the specificities of the study design and data characteristics. The complete analysis focused on the EEG-based outcome measures, with an emphasis on Spectral Power (primary outcome) and Spectral Entropy (secondary outcome), across the Delta frequency band.

Special attention was given to the Delta frequency band as it is widely recognized for its relevance in neonatal brain activity [99–100]. The Delta frequency band, typically ranging from 0.5 to 4 Hz, is the slowest of the EEG frequency bands and is a critical marker of brain maturation. Higher absolute power in the delta frequency band has been associated with more favorable long-term neurodevelopmental outcomes, reflecting the progression of underlying neural processes during early development [99]. Given its prominence in this context, we believe that the Delta frequency band can be an essential marker for assessing the impact of sound and music on the neurophysiological state of our participants, providing in result critical insights into how these infants process auditory stimuli and the extent to which our intervention influences brain activity patterns.

More specifically to the design of our statistical analysis process and given the study’s repeated measures design and the nested data structure (with multiple observations per infant), a mixed-effects model was decided to be employed to analyze first the Delta Spectral Power, allowing for the inclusion of both fixed effects (conditions and facilitators) and random effects (variability across individual infants), while also meticulously fitting the model to account for the inter-individual variability after isolating the impact of the different intervention conditions and facilitator profiles.

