Furthermore, by employing electroencephalography (EEG) and utilizing a custom-made and adapted EEG (pre)processing pipeline, the effects of our live singing intervention on premature infants can be studied in greater detail. This advanced neuroimaging approach allows for a nuanced understanding of how different auditory stimuli influence brain activity in this vulnerable population. As discussed in previous work [30], neuroimaging-guided interventions should be more extensively introduced in the NICU because they can provide real-time insights into the brain’s response to external stimuli, capturing dynamic changes that might not be observable through behavioral measures alone. In this regard, our protocol not only enhances the precision of our study but also contributes to the development of more tailored applications in the future, optimizing music-based interventions to suit the unique neurodevelopmental needs of each infant in the NICU.

Finally, it is important to point out that the study design we decided to implement includes the chosen variety of caregivers to allow us to provide a more comprehensive insight into the role of emotional and social factors evident and embedded in the treatment process of premature infants in real-world situations and environments. For that matter, on the one hand, the inclusion of both parents in the protocol ensures that the study captures potential sex-specific effects, which could be related to differences in voice register or emotional bonding, while, on the other hand, incorporating professional music therapists as facilitators offers a standardized comparison to the former set of caregivers, helping to differentiate the effects of kinship as well as musical and clinical expertise related to the implementation of music-based interventions in this sensitive context. This diversity in caregivers could not only enrich the study’s findings but may also enhance the generalizability of its results, ultimately leading to more comprehensive recommendations for NICU music-based interventions.

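### The hypotheses concern F0, kinship and their interaction, but the analysis tests only a four-level facilitator label: the three effects are never tested separately, sung F0 is never tested, and kinship coincides with profession.

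*Protocol article*

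**What the plan says.** - **Study objectives.** The question is whether four facilitators, characterised by F0 and kinship, leave different short-term EEG responses. H1 sets the "mother (high fundamental frequency – biological kinship) compared to the father (low fundamental frequency – biological kinship" and also against the two music therapists. H0 reads "We assume that there is no interaction between the fundamental frequency and the kinship profile (mother, father, man, woman" and adds that "neither the fundamental frequency nor the human profile has a primary effect".
- **The fundamental frequency of singing.** F0 is presented as an objective physical measure that goes with sex: "male voices typically having a lower F0 – around 100–120 Hz", against roughly 200–220 Hz for women.
- **Intervention.** In NoteA every facilitator repeats the note A "at any possible and convenient to them frequency that corresponds to this specific note"; the octaves listed run from A2 (110 Hz) to A5 (880 Hz).
- **Outcomes and statistical analysis.** The mixed model has "fixed effects (conditions and facilitators) and random effects (variability across individual infants"), followed by LSD pairwise tests. No F0 term, kinship term or difference of differences is named.
- **Primary outcomes.** The results are a 3-df facilitator test, F(3,88) = 3.627, p = 0.016, a condition test, F(4,88) = 1.669, p = 0.164, and selected pairs.
- **Discussion.** Having therapists beside parents is described as "helping to differentiate the effects of kinship as well as musical and clinical expertise".

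**The concern.** The four facilitators form a 2x2 layout: female or male voice, by related parent or unrelated therapist. The hypotheses are written in terms of that layout, but the analysis treats the four cells as an unstructured label. A significant facilitator test shows that some cell differs. It does not show whether voice, kinship or their combination is responsible.

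Two features of the design add to this:

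- F0 is not fixed during NoteA, so sex is only a proxy for the quantity the title question is about.
- Both related singers are parents and both unrelated singers are professional music therapists, one of each sex. No analysis can separate kinship from profession in these data.

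What is at stake is interpretation. The Discussion already explains the father's result in the Song condition by lower-pitched sound, although no test of F0 stands behind that explanation.

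**Working it through.** **Inputs.** Table 3 facilitator means (µV²): mother 707.362, father 393.818, male therapist 297.398, female therapist 131.442. The therapist rows are identified from the Results text, which gives the female therapist the lowest power. Residual variance (scale parameter) s² = 404,270.98. There are 100 observations = 5 infants x 4 facilitators x 5 conditions, so 25 per facilitator.

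**1. Which model was fitted.** Residual df for additive facilitator and condition effects with infants: 100 − 1 − 3 − 4 − 4 = 88, as printed. A facilitator-by-condition term would leave 76. The fitted model therefore has a four-level label and no F0 or kinship term.

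**2. Reproducing the reported test.** The mean of the four means is 382.505. F = 25 x Σ(mean − 382.505)² / (3 x s²) = 3.627, p = 0.016. The LSD p-values for the mother also reproduce, with SE = √(2s²/25): against the female therapist 0.002, the male therapist 0.025, the father 0.085.

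**3. Splitting the 3 df.** For weights w, estimate = Σw·mean and SE = √(s² Σw²/25).

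| Contrast | Arithmetic | Estimate | SE | t | F | p (88 df) |
|---|---|---|---|---|---|---|
| Female − male voice | (707.362 + 131.442)/2 − (393.818 + 297.398)/2 | 73.8 | 127.2 | 0.58 | 0.337 | 0.56 |
| Parent − therapist | (707.362 + 393.818)/2 − (131.442 + 297.398)/2 | 336.2 | 127.2 | 2.64 | 6.989 | 0.010 |
| Interaction | (707.362 − 393.818) − (131.442 − 297.398) | 479.5 | 254.3 | 1.89 | 3.555 | 0.063 |

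Check: (0.337 + 6.989 + 3.555)/3 = 3.627, the reported omnibus F. About 64% of the facilitator sum of squares (6.989/10.88) lies in parent versus therapist and about 3% in voice sex.

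**4. The average hides the singing conditions.** Three of the five conditions are silence. From Table 2, female minus male voice is:

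- NoteA: (1381.3 + 276.1)/2 − (657.1 + 273.6)/2 = +363
- Song: (213.4 + 79.1)/2 − (574.2 + 270.2)/2 = −276

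With the pooled residual the SE of each is √(404,271/5) = 284, so neither is distinguishable from zero. The signs are opposite, however, and 73.8 is an average over them and over silence.

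**5. Sex as a proxy for F0 in NoteA (assumed figures).** Suppose all women sing A3, and code A2 = 0 and A3 = 1 on the log2 scale. If no man sings A3, sex explains all the variance in log2 F0. If a quarter do, it explains 60%: between-sex variance 0.1406, within-sex 0.0938. If half do, it explains 33%: 0.0625 against 0.125. The documents do not say which of these is nearest.

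**6. Kinship and profession.** Related singers are mother and father, called untrained in Study design and given 30 minutes of training under Intervention. Unrelated singers are both professional music therapists. There is no untrained unrelated singer and no professional related one as a design category, so the two factors share one contrast.

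**The case against.** A reader might infer that the facilitator test says nothing about H0 and that H1 goes untested. The documents do not support that. H0 denies the interaction and both main effects. With F0 read as voice sex, as H1 reads it, this is the statement that all four facilitator means are equal, which the 3-df test does test. H1 compares the mother with each other singer, and the LSD pairs are those comparisons: mother against father is a sex difference among parents, and mother against female therapist is a parent-therapist difference among women. The four-level factor is also a saturated 2x2, so the contrasts can be had from the same model. Listing contrasts is often left to an analysis plan, and the study calls itself exploratory.

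These arguments narrow the point without removing it. The article states its model, fits it and reports only the omnibus test and pairs, while its question and its Discussion speak of F0 and kinship.

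Three further readings are tempting and not supported:

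- *That the preliminary data show no F0 effect.* The 95% interval for 73.8 is about −179 to +327. It comes from five infants, uses sex as proxy, and averages over silence and over opposite signs.
- *That the high and low labels actually failed.* Free octave is stated for NoteA only. The typical male and female values lie near A2 and A3, so convenient octaves may follow sex. Overlap is allowed, but it has not been shown.
- *That loudness must be adjusted for.* The article says "a dB measuring device will be also stationed in the dedicated room", for monitoring. It does not report that level differed between the four voices, and level may be part of how a voice acts.

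**Conclusion.** The point holds in limited form. The joint null is tested if sex is accepted as the proxy for F0, and the mother's pairs address H1. The separate F0, kinship and F0-by-kinship effects are neither specified nor reported, and F0 as a physical quantity is never tested. Kinship is completely confounded with profession, so the claim to help differentiate kinship from expertise is wrong whatever the sample size.

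The practical size shows in the preliminary data: the significant facilitator result is mainly a parent-therapist difference (336.2, p = 0.010), with voice sex at 73.8 (p = 0.56) and the interaction at 479.5 (p = 0.063). A reader of the Results section cannot learn this. These figures take the article's own error term and 88 df at face value, come from five infants with very dispersed data, and average over silence, so they are illustrative only. The stated sample size is not at issue here. The analysis should be changed, but the data collection need not be.

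**What to change.** 1. Prespecify three 1-df contrasts from the facilitator factor: female versus male voice, parent versus therapist, and their interaction. Use these in place of reliance on the omnibus test and all-pairs LSD tests.
2. Give the same contrasts for the singing conditions. An additive model cannot do this, so either add a facilitator-by-condition term or fit the singing blocks alone.
3. Label the first contrast as voice sex (proxy for F0) and the second as related parent versus unrelated professional therapist. Drop the claim to separate kinship from expertise.
4. If the video carries sound, report measured F0 for each singing block and use it in a supporting analysis restricted to singing blocks. It will be close to collinear with facilitator wherever octave follows sex. If there is no usable sound, word the conclusions as facilitator differences (sex, and kinship with profession) and not as F0 effects.

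Items 1 to 3 cost a few lines of text and code. Item 4 costs some audio processing and depends on recordings whose content the article does not state. Nothing changes in the intervention, the sessions or the number of infants.

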## Methods

### Study design

Between 06.2023 and 12.2025, all premature newborns who meet the specific inclusion criteria (detailed below) in the NICU of the ‘Panagiotis and Aglaia Kyriakou’ Children’s Hospital in Greece will be screened, and those who qualify will be invited to participate in this exploratory study. During their stay in the NICU, this group of premature infants will be exposed to a structured live singing intervention – including varying investigative conditions of silence and singing – for four days within one week. In terms of measurements, electroencephalography (EEG) will be used to record the newborns’ brain activity throughout their participation in the exploratory study, while video data will be also recorded, forming an auxiliary part to the EEG data collection process. Blinding of the intervention is difficult to implement in this research context due to the direct involvement of parents and facilitators in delivering the singing intervention, which makes it challenging to conceal the nature of the intervention from those administering or receiving it. Based on all the above, the schedule of enrollment, intervention and assessment can be seen in Fig 1 while a flowchart of the study design is shown in Fig 2.

**Fig 1 pone.0328211.g001:**
[figure not shown]
Schedule of enrolment, intervention and assessment.

**Fig 2 pone.0328211.g002:**
[figure not shown]
Study Protocol Flow Chart.

In this design, although the EEG will be the primary tool of data collection and analysis, the rationale for incorporating video data is multifaceted. Firstly, the video recordings will complement the electroencephalogram (EEG) recordings in offering a comprehensive parallel view of the infants’ neural and behavioral responses. Furthermore, the videos will serve as a tool for quality control by ensuring that the prescribed research protocol is uniformly followed by all facilitators, contributing to the scientific integrity of the research. Finally, the videos will allow for a later examination of any synchrony or coordinated interactions between the infant and the facilitator, shedding light on phenotypical – not able to be measured by the EEG – aspects of the intervention.

The live singing intervention will be delivered by four different profiles of individuals-facilitators: a male music therapist, a female music therapist, the mother, and the father of the newborn. During the delivery of the intervention (explained in more detail below), there will be five ‘conditions’ measured: Silence1 (180 seconds), Note A (60 seconds), Silence2 (180 seconds), Song (90 seconds) and Silence3 (180 seconds).

It is important to note that the study protocol will be conducted in a dedicated room, largely isolated from the ambient noise typically found in the rest of the NICU. This aspect of the study design is crucial for two main reasons:

Firstly, it will ensure the comfort and safety of the participating newborns. All actions taken in the context of the NICU require adherence to the recommended standards for the NICU sound environment. Therefore, the importance of a well-managed acoustic environment in reducing stress and discomfort for our participating infants is of paramount importance. Such a consideration has been consistently highlighted both for clinical and research settings alike [32] and a sound-controlled room within the NICU seems to be the only viable option for achieving the necessary level of sound management for our participants, without disrupting other clinical operations. More specifically, in the NICU context, when considering the operational sound as outlined by White, Smith, Shepley, et al. [31], the combination of continuous background sound and operational sound should not exceed an hourly L_eq_ of 45 dB and an hourly L_10_ of 50 dB, both A-weighted slow response, with transient sounds or L_max_ not exceeding 65 dB. Our study, with sound exposure lasting less than 3 minutes per hour, will strictly adhere to these guidelines. However, the transient nature of singing, distinct from the continuous and better-controlled sound pressure levels typically found in continuous speech, might lead to brief instances where we slightly exceed these thresholds by about 15 dB. According to evidence, even professional singers, and more so untrained individuals like the parents participating in our study, are not able to produce transient peak Sound Pressure Levels (SPLs) below 78–79 dB when singing softly [70]. However, it has been noted that in environments with lower ambient noise, humans can more easily maintain a soft vocal output because the reduced background sound allows for greater control and minimizes the need to compensate with higher volume [71]. Therefore, we believe that a dedicated room will significantly aid in ensuring the correct application and viability of the aforementioned recommendations – by providing an acoustically controlled setting that minimizes ambient noise and facilitates softer singing performance – as compared to the open NICU floor, thus preventing the intervention from inadvertently exceeding the recommended soundscape limits.

Secondly, recent research, including a study by Restin et al. [72], indicates that incubators can be significant sources of noise, especially in the open environment of the NICU floor. To mitigate this issue, we plan to use an open cot/radiant warmer (as depicted in Fig 3) in the dedicated room when applicable, or alternatively, bring the entire incubator into the room. This approach will help minimize or eliminate noise from the incubator that might reach the infant. As an additional precaution to all the above, a dB measuring device will be also stationed in the dedicated room, outside the incubator where applicable, to monitor noise levels throughout the intervention.

